## Abstract

**Background:**

Adverse childhood experiences increase the risk for psychological disorders and lower psychosocial functioning across the lifespan. However, less is known about the processes through which ACE are linked to multiple negative outcomes. The aim of the FACE epidemiological study is to investigate emotion regulation (emotional reactivity, perseverative thinking and self-efficacy for managing emotions) and social information processing (rejection sensitivity, interpretation biases and social understanding) as potential mechanisms linking adverse childhood experiences and psychosocial functioning in a large population sample of young adults. It is embedded in a larger project that also includes an ecological momentary assessment of emotion regulation and social information processing and informs the development and evaluation of an online self-help intervention for young adults with a history of ACE.

**Methods:**

The study plans to recruit 5000 young adults aged 18 to 21 from the German-speaking Swiss population. Addresses are provided by Swiss Federal Statistical Office and participants are invited by mail to complete a self-report online survey. If the targeted sample size will not be reached, a second additional sample will be recruited via educational facilities such as universities or teacher training colleges or military training schools. Three follow-ups are planned after 1 year, 2 years and 3 years, resulting in ages 18–24 being covered. The main exposure variable is self-reported adverse childhood experiences before the age of 18, measured at the baseline. Primary outcomes are psychosocial functioning across the study period. Secondary outcomes are social information processing, emotion regulation and health care service use. Statistical analyses include a range of latent variable models to identify patterns of adverse childhood experiences and patterns and trajectories of psychosocial adaptation.

**Discussion:**

The results will contribute to the understanding of the underlying mechanisms that link ACE with psychosocial functioning which is crucial for an improved insight into risk and resilience processes and for tailoring interventions. Furthermore, the identification of factors that facilitate or hinder service use among young adults with ACE informs healthcare policies and the provision of appropriate healthcare services.

*Trial registration number*: NCT05122988. The study was reviewed and authorized by the ethical committee of Northwestern and Central Switzerland (BASEC number 2021-01204).

## Background

Childhood experiences affect psychosocial functioning and mental health across the life course for better or worse. Positive family experiences and social support promote high well-being and represent a buffer against stressors. Still, one out of three children growing up worldwide experiences adverse childhood experiences (ACE) such as emotional, physical and sexual abuse, emotional and physical neglect, exposure to intimate partner violence or other household dysfunctions [1]. A recent review of meta-analyses found worldwide self-reported prevalence rates of 36.3% for emotional abuse, 22.6% for physical abuse, 12.7% for sexual abuse (18% for girls and 7.6% for boys), 18.4% for emotional neglect and 16.3% for physical neglect [1].

ACE are a well-established transdiagnostic risk factor for impaired psychosocial functioning and various mental and physical health conditions throughout life. This includes depression, anxiety, post-traumatic stress disorder (PTSD), suicidal behaviour, obesity, cardiovascular diseases, and other medical conditions [2–4]. However, less is known about the processes through which ACE are linked to multiple negative outcomes. A better understanding of the underlying processes is crucial for an improved insight into risk and resilience processes across the lifespan.

In the context of ACE, emerging adulthood, covering the ages of 18 to about 25 years, is a crucial stage in life that offers a window of opportunity for recovery, but also holds a risk for the consolidation of problems, deterioration of trajectories or the onset of destructive outcomes. Young adults start to take control of their own lives and are better able to distance themselves from an adverse family environment [5]. Self-regulation capacity and executive functioning increase and facilitate planning ahead and the consideration of alternatives [6]. Multiple transitions occur, including the shift from economic dependence to independence, moving out of the parents’ home, forming new relationships, and entering new stages of professional or educational life [7]. These transitions offer turning points and opportunities for redirecting maladaptive trajectories into healthier paths, but also pose challenges to the psychosocial adaptation of young adults [5, 8, 9]. Insights into such trajectories and their underlying processes is critical to inform interventions targeting risk factors for the negative effects of ACE in emerging adulthood.

Processes linking ACE with psychosocial functioning may depend on the subtype of ACE. ACE represent distinct experiences such as physical, emotional or sexual abuse, neglect, or household dysfunctions such as parental substance use or psychopathology which can have different consequences on physical and psychological health and psychosocial adaptation. However, different definitions of ACE and the fact that ACE often co-occur [2] hinder the integration of results. The analysis of the effects of ACE traditionally employs a single risk approach, examining only one subtype of ACE and ignoring the high co-occurrence of ACE, or use a cumulative risk approach, summarizing different forms of ACE and not accounting for the fact that ACE represent distinct experiences [10]. A more recent development addressing this issue is the Dimensional Model of Adversity and Psychopathology (DMAP) by McLaughlin, Sheridan and colleagues [10–13] which conceptualises ACE within underlying dimensions of adversities. These dimensions are the level of threat associated with abuse and level of deprivation associated with a lack of cognitive inputs or social stimulation as well as neglect. These dimensions have a differential impact on cognitive and emotional development. The exposure to threat in early life has been linked with higher perceptual sensitivity and attention biases towards negative emotional stimuli and patterns of information processing that prioritise threat-related information, higher emotional reactivity, and poor emotion regulation. Deprivation has been associated with impaired cognitive learning, i.e., in the domain of language and executive functioning.

### Mechanisms linking ACE and psychosocial functioning

The present study focuses on two important mechanisms also posited in the DMAP that are known to be affected by ACE and are risk factors for psychosocial adaptation and psychological disorders later in life: emotion regulation and social information processing. Deficits in *emotion regulation* has been established as a direct risk factor for psychological disorders and as a mechanism that mediates the relation between ACE, psychosocial functioning and different mental health problems [9, 14–19]. Higher emotional reactivity, rumination, and less adaptive emotion regulation strategies, as well as ineffective responses to distress, link ACE with internalising and externalising psychopathology in adolescence [16, 20]. *Social information processing,* including rejection sensitivity, social interpretation biases and social understanding have been found to link ACE to a lower psychosocial functioning. ACE deprive children and adolescents of socio-emotional support within the family and represent pathogenic relational experiences in an environment which is supposed to give care. Attachment theories point out that this can result in an insecure or disorganised attachment style, dysfunctional internal working models of the self, of others and of how relationships work which are risk factors for later psychological disorders [21, 22]. Internal working models provide an inadequate basis for appropriate social information processing and hinder engagement in good social relationships.

Rejection sensitivity, i.e., the tendency to anxiously expect, perceive and overreact to social rejection, attention and interpretation biases, as well as social understanding in tandem with emotion regulation, play an important role in social functioning, affect tendencies to approach or withdraw from others and reactions of interaction partners [23, 24]. Rejection sensitivity has been confirmed as a mediator for the associations between emotional abuse and depressive symptoms in adulthood [23–26]. Studies investigating social understanding, hostile attribution bias and attention biases in individuals with a history of ACE have yielded inconsistent results [27]. Negative interpretation biases were found to mediate the association between rejection sensitivity and depressive symptoms [28].

Theory and empirical findings suggest that maladaptive internal working models, interpretation biases and rejection sensitivity can lead to less favourable social behaviour that hinders the building up of good relationships and seeking social support [22]. Maltreated children are at risk for social withdrawal, aggressive behaviour or both [29, 30] and a history of ACE is linked to lower social motivation, less social support and higher social isolation in adults [31, 32]. Lower social support and loneliness have been established as a mechanism linking ACE to adolescent or adult well-being and psychopathology [32–37].

Apart from social support, professional help is an important factor that can mitigate the consequences of ACE on psychosocial functioning in young adulthood. However, many individuals who meet the criteria for psychological disorders do not seek or receive treatment [38]. There is a lack of knowledge on factors and processes that determine whether someone seeks, receives, and accepts social and professional support, especially among individuals with a history of ACE. Therefore, identifying the facilitating and hindering factors for receiving treatment and service use among young adults with ACE can help to improve access to appropriate interventions and promote the use of mental healthcare services.

### The present study

The present study aims to overcome several shortcomings of previous studies and theoretical models: Firstly, while most theoretical models and empirical studies have focused either on emotion regulation or social information processing, the FACE study combines these two strands of research and investigates the longitudinal interplay and relative strength of emotion regulation and social information processing as mediators for the link of ACE and psychosocial functioning. This is relevant, as the intensity of emotions and emotion regulation may affect different social information processing tasks. Lemerise and Arsenio’s Integrated Model of Emotion Processes and Cognition in Social Information Processing [39] posits that a database of memories, social schemas, social knowledge and acquired rules as well as the intensity of emotions, emotional processing and emotion regulation affect all stages of social information processing, including the perception and encoding of cues, their interpretation, the clarifications of goals, and finally the behavioural response. These factors may affect good social relationships and seeking and receiving social support.

Secondly, while many previous studies ignore the subtypes of ACE as potential moderators for differential health outcomes and employ a single risk or a cumulative risk approach, the FACE epidemiological study uses comprehensive measures for assessing distinct patterns of ACE. This may provide a better understanding of more complex risk environments [40]. Such patterns could then be related to patterns of psychosocial adaptation, such as vulnerable, resilient or average psychosocial functioning. Complementary to this categorical approach, we will investigate a dimensional approach to vulnerability and resilience which defines resilience as “doing better than expected” compared to individuals with similar levels of adversity [41, 42].

Thirdly, the FACE epidemiological study uses a longitudinal design complemented by an ecological momentary assessment in a large population-based sample which can disentangle the short- and long-term temporal interplay of emotion regulation and social information processing. It thus provides a better understanding of the mechanisms underlying the association between ACE and psychosocial functioning.

In sum, the major aim of this study is a comprehensive analysis of processes and mediators that link ACE and psychosocial functioning in emerging adults in the framework of the Integrated Model of Emotion Regulation and Social Information Processing in the Aftermath of ACE (see Fig. 1). Furthermore, we aim to identify factors that facilitate or hinder the use of mental healthcare services and finding social support among young adults with history of ACE.

**Fig. 1 Fig1:**
[figure not shown]
Overview of the Integrated Model of Emotion Regulation and Social Information Processing in the Aftermath of ACE

## Methods

### Objectives

The primary objective of the study is to examine the impact of self-reported ACE on psychosocial functioning and to investigate the longitudinal interplay and relative strength of emotion regulation and social information processing, as processes and mediators linking ACE with psychosocial functioning in young adults in the framework of the Integrated Model of Emotion Regulation and Social Information Processing in the Aftermath of ACE. A multivariate approach will identify distinct adaptation patterns of psychosocial functioning, such as chronic maladaptive, intermittent maladaptive, resilient and recovery trajectories [43, 44]. The main hypotheses are that ACE are associated with a higher risk for lower psychosocial functioning in young adulthood and that this association is mediated by (a) deficits in emotion regulation, i.e., higher emotional reactivity, more perseverative thinking and lower self-efficacy for managing emotions, and (b) social information processing, i.e., higher rejection sensitivity, higher levels of interpretation biases and lower social understanding. Referring to the DMAP, we expect that emotion regulation shows a stronger indirect effect for the association between the threat dimension of ACE and psychosocial functioning than for the association between the deprivation dimension of ACE and psychosocial functioning. Furthermore, the FACE epidemiological study aims to identify factors that facilitate or hinder the use of mental healthcare services among young adults with history of ACE.

Secondary objectives are to analyse the effects of emotion regulation and social information processing on the quality of friendships and social support; to explore the longitudinal associations of emotion regulation and social information processes on facets of psychosocial functioning and distress and to investigate the longitudinal associations between emotion regulation and social information processing. Additional explorative analyses investigate differential effects of distinct patterns of ACE on emotion regulation and social information processing as well as psychosocial functioning. Figure 1 gives an overview of the assessed variables and the hypothesised associations between them.

### Study design

The FACE epidemiological study consists of an accelerated cohort design with four waves, which allows to cover the development between the ages of 18–24 years within a three-year investigation. Participants fill out online self-report questionnaires at baseline (2021; w1) and in three yearly follow-ups (2022: w2, 2023: w3, 2024: w3).

The FACE epidemiological study (subproject A in Fig. 2) is embedded in a larger project that also includes the development and evaluation of an online self-help intervention for young adults with ACE (subproject B). The self-help intervention targets self- and emotion regulation and social skills and information processing and will be evaluated in a randomised clinical trial (RCT). Subproject B also includes an ecological momentary assessment study to provide real-life data for testing the efficacy of the intervention and further investigating the interplay of ACE, emotion regulation and social information processing. The epidemiological study informs the development of the intervention and identifies young adults with ACE who will be invited to take part. The later waves of the epidemiological study will serve as a long-term follow up for the intervention and allow a comparison to young adults with ACE who were not willing to take part in the intervention. A detailed study protocol for subproject B will be published in due course.

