### Statistical analysis

Significance level will be two-sided α = 0.05. Due to the large sample size, effect sizes will be prioritised over the significance level for the interpretation of the results. Cohort data will be analysed with a range of observed and latent variable models using Mplus that include person- and variable-centred approaches. Distinct patterns of ACE will be identified using a Latent Class Analysis based on the subtype and frequency of childhood experiences, for example patterns combining subtypes of child maltreatment, household dysfunctions or bullying by peers. Psychosocial functioning as primary outcome will be analysed in a variable- and a person-centered approach. For the variable-centered approach, a composite measure of psychosocial functioning will be computed using Factor Analyses including bifactor models. For the person-centered analyses, a Latent Profile Analysis is used to identify psychosocial adaption patterns, for example an average group, a resilient group, a moderately vulnerable group, and a highly vulnerable group.

The main hypotheses for the associations between childhood experiences, emotion regulation, social information processing and psychosocial functioning will be analysed using structural equation models with subtypes, dimensions, or patterns of childhood experiences as predictor and moderator variables and psychosocial functioning as outcome variable. (Moderated) mediation hypotheses will be tested using structural equation modelling with the simultaneous inclusion of dimensions of emotion regulation and social information processing variables as mediators linking childhood experiences with psychosocial functioning.

The trajectories of psychosocial adaptation, emotion regulation strategies and social information processing will be investigated with Growth- and Growth-Mixture models. For the longitudinal trajectories of psychosocial functioning across emerging adulthood, we expect to find a chronically dysfunctional group, a recovering group and a resistant trajectory group over time using Latent Growth Mixture Models. The effect of the use of mental health care services after baseline will be analysed with a Latent Transition Analysis where service use will be entered as predictor and the transition between the subgroups as outcome variable.

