Logistic regression analyses will be used to analyse predictors of service use and enrolment to the FACE intervention (as binary variables). Predictor variables are simultaneously entered in the model and include ACE, age, gender, socio-economic status and psychosocial functioning.

Where an influence of the COVID-19 pandemic is to be expected, we will adjust for the impact of the crisis on individuals to ensure that trends are not created by the consequences of the COVID-19 epidemic or conduct sensitivity analysis to gauge the effect of the COVID-19 crisis. For example, there may be a general improvement of mental health in case the pandemic is ending between two waves of our study, and it will be important to account for that when considering trends across the four waves.

*Justification of sample size:* The sample size of the epidemiological study is determined with consideration of the number of participants needed in the FACE intervention study, i.e., 350 participants. This sample size allows the detection of small effect sizes for the interaction between time (pre, post, follow-up) and the two treatment condition SSIP vs SER, mediation analyses with parallel mediators in a structural equation modelling framework and, a multi-group model for each treatment arm, and an accurate estimates of the regression coefficients, the variance components and the standard errors for multilevel analyses of the EMA data [75, 76], details will be reported elsewhere]. For the FACE *epidemiological study*, the sample size of 5000 at baseline is based on the expectations that 25% (n = 1250) of the participants report ACE and that a third of them (n = 375) give an informed consent for the intervention study and start the FACE self-help programme.

*Handling of missing data:* An attrition of 40% is expected in the fourth wave of the epidemiological study, resulting in a sample of about 3000 participants at the fourth wave. We will conduct missingness analyses which identify patterns and predictors of missingness and determine whether missing data are completely at random, at random or non-ignorable. If missingness at random is supported, we will use Multiple Imputations in Mplus [77]. Sensitivity analyses will compare the results of different ways of imputing missing data including complete case analyses and if appropriate full information maximum likelihood.

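### About 30% of ACE-exposed participants are expected to start the project's own programme on the hypothesised mediators, and the longitudinal models do not account for it

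*Protocol article*

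**What the plan says.** The protocol article places the cohort inside a larger project with a randomised evaluation of an online self-help programme. On recruitment, Study design says: "The epidemiological study informs the development of the intervention and identifies young adults with ACE who will be invited to take part". On content, it says: "The self-help intervention targets self- and emotion regulation and social skills and information processing". It adds that later cohort waves double as the programme's long-term follow-up, so enrollees remain in the cohort data.

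The sample-size paragraph under Statistical analysis gives the numbers. For the cohort, "the sample size of 5000 at baseline is based on the expectations that 25% (n = 1250) of the participants report ACE", and "a third of them (n = 375) give an informed consent for the intervention study and start the FACE self-help programme". The paragraph names "the two treatment condition SSIP vs SER" as the conditions and mentions no untreated arm.

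Objectives and Statistical analysis make emotion regulation and social information processing the mediators between ACE and psychosocial functioning. Trajectories are to be studied with growth and growth-mixture models, where "we expect to find a chronically dysfunctional group, a recovering group and a resistant trajectory group over time". A latent transition analysis takes mental health service use after baseline as its predictor. FACE enrolment appears in the analysis section only as the outcome of a logistic regression. The one external influence for which the section announces adjustment or sensitivity analysis is COVID-19. The limitations in the Discussion cover self-report bias, COVID-19 and selective attrition, but not the programme.

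**The concern.** Receipt of the programme is tied to the main exposure, and the programme is built to change the variables through which that exposure is hypothesised to act. A cohort model that ignores it estimates, after enrolment, a mixture of what follows from ACE and what follows from ACE plus treatment of nearly a third of the exposed.

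If treatment helps and the benefit lasts, three results are exposed. The ACE-to-mediator path shrinks, and the indirect effect with it. The ACE-to-functioning path shrinks. Some people classified as recovering, or as moving to a better-functioning class, would be there because of the programme.

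This matters because the plan puts effect sizes ahead of significance when interpreting results, and effect sizes are what would be distorted. The Discussion also expects the longitudinal data to inform causal mechanisms. COVID-19, which the plan does address, touches the whole cohort. The programme touches only the exposed part.

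**Working it through.** **Inputs from the article (sample-size and missing-data paragraphs).** Baseline N = 5000; 25% with ACE; one third of these, given as n = 375, start the programme; 350 needed in the intervention study; 40% attrition by the fourth wave.

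**Reproducing the plan's figures.**
- ACE group: 5000 × 0.25 = 1250. Agrees.
- Starters: 1250 / 3 = 417, not 375. The stated n is 375 / 1250 = 30%. The wording and the number differ slightly; I use 30%.
- Needed for the trial: 350 / 1250 = 28%.
- Share of whole cohort: 375 / 5000 = 7.5%.
- Fourth wave: 5000 × 0.60 = 3000. Agrees.

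**Shift in the ACE-group mean.** The article gives neither a programme effect nor an ACE gap, so both are assumed. Let d be the programme's lasting effect on a mediator in SD, the same for every starter, and let the ACE gap be 0.5 SD.
- Shift = 0.30 × d.
- With proportional attrition, the fourth wave has 750 ACE (225 treated) and 2250 non-ACE participants. SE of the group difference = √(1/750 + 1/2250) = 0.042 SD.

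| d | Shift (SD) | Shift / SE | Share of 0.5 SD gap |
|---|---|---|---|
| 0.1 | 0.03 | 0.7 | 6% |
| 0.2 | 0.06 | 1.4 | 12% |
| 0.3 | 0.09 | 2.1 | 18% |
| 0.5 | 0.15 | 3.6 | 30% |

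The relative size depends on the assumed gap. At d = 0.2 the share is 20% of a 0.3 SD gap and 9% of a 0.7 SD gap.

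**Indirect effect.** With an assumed mediator-to-outcome coefficient of 0.4, the indirect effect is (0.5 − 0.30 × d) × 0.4. This is 0.200 at d = 0, and 0.176, 0.164 and 0.140 at d = 0.2, 0.3 and 0.5: losses of 12%, 18% and 30%. A large-sample simulation gave 0.177, 0.164 and 0.139. When people with worse mediator scores enrolled more often, it gave 0.175, 0.164 and 0.141, so this form of self-selection hardly changes the result.

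**Differential retention.** If starters stay at 80% or 100% while the ACE total at the fourth wave remains 750, the treated share becomes 300/750 = 40% or 375/750 = 50%, and the shift grows in proportion.

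**The case against.** The strongest reply is that this is silence in a condensed article. No passage says enrollees will be pooled without distinction, and the article gives no covariate list for any structural equation or growth model. The overlap is acknowledged: Study design foresees comparing participants with ACE-exposed people unwilling to take part, and enrolment is modelled as a binary variable, so the data will be there. The transition analysis also has service use as a predictor.

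Part of this stands. The omission is not a misstatement, and nothing prevents the authors from handling it. But an ordinary missing covariate differs from a treatment that the project itself delivers to exposed members only. The comparison with unwilling participants evaluates the programme; it does not take its effect out of the cohort models. The service-use items in Table 1 do not list FACE, the logistic regressions treat service use and FACE enrolment as separate outcomes, and the transition analysis is only one of the affected models.

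The reply is right on several limits. A reader might infer that every follow-up is contaminated. The article does not date the programme, so that is not established. A reader might also take the bias as certain. It depends on a lasting effect that the article does not quantify, and the calculation gives each starter the full effect. ACE also enters the models as subtypes, dimensions or patterns, so a shift in a two-group mean does not map directly onto every coefficient. Finally, the objectives do not use the term natural course.

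**Conclusion.** The gap is real and follows from the plan's own statements: 375 of 1250 ACE-exposed participants (30%) are expected to start a programme aimed at the mediators, they remain in the later waves, and no longitudinal model deals with it.

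The consequence is conditional. If the programme has a lasting benefit, post-enrolment ACE-to-mediator and ACE-to-functioning paths would be attenuated, by roughly 12% to 30% for effects of 0.2 to 0.5 SD against an assumed 0.5 SD gap, and part of a recovering class could be treatment. At 0.1 to 0.2 SD the shift is 0.7 to 1.4 standard errors at the fourth wave, so it may be modest. Wave-1 analyses are unaffected.

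The documents do not show that all follow-ups are affected, that bias will occur, or that enrollees' later data must be dropped from the primary analysis. Dropping them would itself rest on contestable assumptions.

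**What to change.** State in the analysis plan when enrolment falls relative to the waves. For every longitudinal model that uses post-enrolment waves (mediation, growth, growth-mixture, transition), add:

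1. A sensitivity analysis that censors FACE enrollees' data at enrolment, with multiple imputation or full information maximum likelihood conditional on wave-1 predictors of enrolment.
2. A second that keeps all data and adds a time-varying indicator of FACE participation on mediators and outcome.

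Report class sizes and transitions by enrolment status. Limit conclusions about natural course or causal mechanisms to results that agree across these analyses. Correct the starter figure so that one third and 375 no longer disagree.

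The cost is some extra analysis; the planned logistic regression already requires enrolment status. The censored set loses the later data of about 7.5% of the cohort and 30% of the ACE group. Without any recovery from imputation, and with proportional attrition, the fourth-wave SE would be √(1/525 + 1/2250) = 0.048 instead of 0.042, about 15% larger. It also relies on missingness at random given the wave-1 predictors. The indicator model can introduce bias of its own, because enrolment is itself a consequence of ACE status. That is why agreement across both analyses is the safer basis for a conclusion.
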